## Abstract

**Background:**

While exercise can benefit the health and well-being of people with dementia or mild cognitive impairment, many exercise programs offered to this population are passive, unengaging, and inaccessible, resulting in poor adherence. Motion-based technologies are increasingly being explored to encourage exercise participation among people with dementia or mild cognitive impairment. However, the impacts of using motion-based technologies with people with dementia or mild cognitive impairment on variables including balance, movement confidence, and cognitive function have yet to be determined.

**Objective:**

The purpose of this study is to examine the impacts of a group motion-based technology intervention on balance, movement confidence, and cognitive function among people with dementia or mild cognitive impairment.

**Methods:**

In this quasi-experimental pre- and posttest design, we will recruit 24 people with dementia or mild cognitive impairment from 4 adult day programs and invite them to play Xbox Kinect bowling in a group setting, twice weekly for 10 weeks. We will require participants to speak and understand English, be without visual impairment, and be able to stand and walk. At pretest, participants will complete the Mini-Balance Evaluation Systems Test (Mini-BESTest) and the Montreal Cognitive Assessment (MoCA). We will video record participants during weeks 1, 5, and 10 of the intervention to capture behavioral indicators of movement confidence (eg, fluency of motion) through coding. At posttest, the Mini-BESTest and MoCA will be repeated. We will analyze quantitative data collected through the Mini-BESTest and the MoCA using an intent-to-treat analysis, with study site and number of intervention sessions attended as covariates. To analyze the videos, we will extract count and percentage data from the coded recordings.

**Results:**

This study will address the question of whether a group motion-based technology intervention, delivered in an adult day program context, has the potential to impact balance, movement confidence, and cognitive function among people with dementia or mild cognitive impairment. The project was funded in 2019 and enrollment was completed on February 28, 2020. Data analysis is underway and the first results are expected to be submitted for publication in 2021.

**Conclusions:**

This study will assess the feasibility and potential benefits of using motion-based technology to deliver exercise interventions to people with dementia or mild cognitive impairment. This work can also be used as the basis for developing specific software and future exercise programs using motion-based technology for people with dementia or mild cognitive impairment, as well as understanding some of the conditions in which these programs can be delivered.

**International Registered Report Identifier (IRRID):**

DERR1-10.2196/18209

## Introduction

### Background

Major neurocognitive disorder, also known as *dementia*, is defined as a significant decline of 2 or more standard deviations from a previous level of performance in 1 or more cognitive domains: executive function, learning and memory, complex attention, language, perceptual-motor abilities, and social cognition [1]. Causes of dementia include Alzheimer disease, cerebrovascular disease, and other conditions that affect the brain [2]. The estimated number of people living with dementia worldwide is 50 million [3], which is predicted to reach 152 million by 2050 [4].

Mild neurocognitive disorder, also known as *mild cognitive impairment* (MCI), is a common precursor to dementia, although not all people with MCI progress to dementia. MCI is characterized as cognitive decline greater than would be expected for a person’s age in 1 cognitive domain that does not interfere with daily activities (eg, leisure) [1]. While MCI is not necessarily progressive, it is estimated that roughly 8.7% of people with MCI progress to dementia each year [5]. There are no pharmacological interventions to reverse cognitive changes or maintain the cognitive functioning of people with dementia or MCI [6]. As such there is an urgent need for effective interventions that support people to live well with dementia or MCI. This includes addressing physical challenges such as falls, which can undermine independence and increase the risk of hospitalization or transfer to long-term care.

People with dementia experience 2 to 8 times more falls than older people without dementia [7]. This has variously been attributed to balance impairments [8], a lack of movement confidence [9], and poor cognitive function or severity of cognitive impairment [10]. Taking balance first, people with dementia or MCI have an increased risk of developing balance impairments compared with older adults without cognitive impairment [11]. Indeed, a study involving people with subjective cognitive impairment, MCI, and Alzheimer disease found that all aspects of balance deteriorated with increasing severity of cognitive impairment [12].

Movement confidence is defined as “a person’s feeling or sense of adequacy in a movement situation” [13] (pg 213). Movement confidence relies heavily on an individual’s implicit belief or perception that they have the skills necessary to successfully perform a movement task [13,14]. Individuals who are movement confident are more likely to participate in movement activities to their satisfaction, whereas nonconfident individuals are less likely to participate in movement activities or find it less satisfying to participate [13,15]. This is important given that an individual’s level of movement confidence relates directly to their engagement with and level of participation in physical activity and exercise [16]. Lack of movement confidence is associated with an increased risk of falling among older adults, in general [17]. Among people with dementia or MCI, lack of movement confidence is prevalent [18,19], although no studies have examined the direct link between lack of movement confidence and risk of falling. Given the above, there is a need for practical interventions that mitigate impairments in movement confidence among people with dementia or MCI. Such interventions could include physical activity and exercise, as these interventions might also impact other areas of physical function, to ensure that older people and people with dementia or MCI have the physical capacity to support the undertaking of higher-risk movements.

Exercise, independent of type (eg, cardiovascular, strength, balance and flexibility), offers a range of benefits, including decreased risk of falls, reduced risk of chronic disease, increased physical function (eg, balance), and improved cognitive function [20]. According to the Ontario Brain Institute [21], people with dementia should follow the same exercise guidelines provided by the Canadian Society for Exercise Physiology for older adults (ie, people aged ≥65 years) [22]. These guidelines recommend participation in roughly 150 minutes of moderate to vigorous physical activity per week, with moderate to vigorous physical activity deemed as activities that produce slight perspiration and a slight increase in breathing rate. It is recommended that for older adults and people with dementia moderate to vigorous physical activity consist of enjoyable activities that include cardiovascular (eg, brisk walking), strength training (eg, lifting weights), and balance exercises (eg, tai chi) [22]. The MCI practice guidelines [23] suggest that exercising twice weekly has benefits for cognition and general health. However, they do not mention the specific duration (ie, number of minutes) or type(s) of exercise to prescribe to people with MCI for optimal health benefits. However, despite the evident benefits of exercise for older people and people with dementia or MCI, only 37.3% of people aged 65 and over in Canada meet the recommended guidelines for exercise participation [24], with these numbers decreasing with advanced age and with the presence of chronic diseases, such as dementia [25]. Technology-based gaming or “exergaming” is emerging as a promising approach to overcome barriers and increase exercise participation by older adults and those with additional needs [26].

Motion-based technology (a type of exergaming technology) operates through human gestures [27]. In motion-based games, actions made in the real world (eg, reaching) are replicated by a virtual character on a screen (eg, a game character grabbing a ball). Motion-based technology has recently grown in popularity as a tool in rehabilitation and scientific research [28] with older adults [29], as well as people with Parkinson disease [30], multiple sclerosis [31], traumatic brain injury [32], and stroke [33]. For example, Pompeu and colleagues [30] showed improvements in balance among people with Parkinson disease after taking part in a 10-week motion-based technology program of 45- to 60-minute sessions 3 days per week involving a series of Nintendo Wii balance games.

A review of the use of motion-based technologies by people with dementia or MCI demonstrated that these technologies can provide enjoyable cognitive, physical, and leisure activities [27]. From a rehabilitation perspective, Schwenk and colleagues [34] showed improvements in balance and fear of falling among people with dementia or MCI after participating in a 4-week virtual reality motion-based technology program held twice weekly. Similarly, Amjad and colleagues [35] showed significant improvements in cognitive function in their participants with dementia or MCI after taking part in a 6-week motion-based technology program, held 5 times per week for 25 to 30 minutes. Moreover, when motion-based technologies are used in a group setting, they allow participants to socialize with and support one another. For example, people with dementia or MCI can play Xbox Kinect bowling “independently together” through cheering, laughing, and friendly competition [36]. Some motion-based systems have additional advantages in terms of accessibility and inclusivity, such as accommodating players who use mobility devices such as walkers and wheelchairs [37].

### Objective

Despite these promising results, the impacts of interventions using motion-based technology are relatively unknown for this population. In their review of the efficacy of motion-based technology interventions for people with dementia with regard to cognition, physical function (eg, strength), emotional well-being, social health, and quality of life, van Santen and colleagues [38] identified only 3 randomized trials. We designed this study to extend knowledge of the potential of motion-based technology in rehabilitation for people with dementia or MCI. Specifically, we will examine the impacts of a group motion-based technology intervention on balance, movement confidence, and cognitive function among people with dementia or MCI. The specific hypotheses of the study reflect these aims. Hypothesis 1 states that balance will show statistically significant improvement after the motion-based technology intervention, as measured by the Mini-Balance Evaluation Systems Test (Mini-BESTest). Hypothesis 2 states that movement confidence will improve after the motion-based technology intervention, as measured by the analysis of coded video-recorded footage taken of participants during the intervention sessions (eg, number of turns completed confidently). Hypothesis 3 states that cognitive function will show statistically significant differences after the motion-based technology intervention, as measured by the Montreal Cognitive Assessment (MoCA).

## Methods

### Study Design

This study will use a standard within-participants design, with measurement at pre- and postintervention (1 group, 2 times).

### Ethics

We received ethical approval to conduct this study from the Health Sciences Research Ethics Board at the University of Toronto (#37326) and from the University Health Network Research Ethics Board (#19-5524), Toronto, ON, Canada. Participants will be able to withdraw their consent to participate in the study at any time by informing the research team in person or using the contact information provided in the informed consent forms. We will not compensate participants for their participation in the study given that they will already be at the day program when the intervention is scheduled to take place, meaning that we do not expect travel-related costs associated with the study. If a participant injures themselves at any point during their participation in the study, we will seek medical attention immediately.

### Participants

We will recruit a convenience sample of 24 people with dementia or MCI from 4 community-based adult day programs. The sample size calculation was based on detecting the minimum clinical important difference of 4.0 points [39] on the primary outcome measure (Mini-BESTest) [40], using an effect size of 0.8, an alpha value of .05, a power value of 80%, and a 2-tailed *t* test. We calculated the estimated sample size to be at least 15 participants, which we increased to 24 participants to allow for 40% attrition. We chose an attrition rate of 40% given that absenteeism and unforeseen events (eg, prolonged illness, moving to long-term care) are common among adult day program clients.

Prospective participants will be required to (1) attend the day program at least twice per week on the days in which the intervention is to be offered; (2) meet the screening criteria for the presence of cognitive impairment (determined by a score of ≤25 on the MoCA); (3) speak and understand English well enough to recognize instructions from the facilitator and respond accurately; (4) not have visual impairment that would prevent the participant to view the game screen; (5) be able to stand and walk, with or without an assistive device (eg, walker), to complete the Mini-BESTest; and (6) have the capacity to provide informed consent, or have a substitute decision maker who can provide informed consent. We will exclude participants who do not meet the above criteria from participating in the study.

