#### Analysis of Test and Questionnaire Data

All analyses will follow an intent-to-treat approach, whereby we will base the results of the experiment on all participants recruited to take part in the intervention, and not just those who complete the intervention [49]. This approach to analysis will provide a more reliable estimate of the true effectiveness of the motion-based technology intervention, by reproducing what occurs in real-world settings such as community-based adult day programs. We will handle missing data using multiple imputation, which is the recommended standard for accounting for missing research data when working with people who have dementia [50]. We will include study site and the number of intervention sessions attended by the participants in the statistical model as covariates. These analyses will be conducted using IBM SPSS version 26 (IBM Corporation), using a *P* value of <.05 and a confidence interval of 95%.

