### Limitations

Despite the suggested contributions of the study, the proposed study features several potential limitations. First, there is a high risk of researcher bias given that the first author (ED) will be the one to conduct all pre- and posttest measures (ie, MoCA and Mini-BESTest), facilitate the study intervention with participants, and assist with analyzing participants’ movement confidence data. Thus, we recommend that future intervention studies of this nature be carried out with a larger research team where different members can be responsible for conducting different aspects of the study (ie, 1 person conducts the pre- and posttest measures, 1 person facilitates the intervention, and at least two separate individuals analyze the movement confidence data). However, from an opposite perspective, it could be considered positive that the first author (ED) was involved in all aspects of this preliminary study, in order to comment on feasibility and effectiveness, which can help to inform future studies of a similar nature.

Second, we will recruit participants via self-referral to a study advertisement, which suggests that participants who volunteer to take part in the study may be more keen to improve their balance, movement confidence, and cognitive function, which could influence their willingness to take part in the intervention.

Third, we expect that 40% of recruited participants will not complete the study intervention due to reasons outside of our control (eg, prolonged illness, moving to long-term care).

Fourth, while this study is adequately powered, the sample size is still considered small. However, small sample sizes are common in many rehabilitation studies due to lack of resources, lack of funding, recruitment challenges, and high dropout rates [53].

Fifth, the demographic questionnaire developed for this study does not capture participants’ specific diagnosis (eg, Alzheimer disease) or the number of years since their diagnosis. Indeed, it cannot be ruled out that these demographic variables could impact participants’ level of movement confidence, as well as their ability to improve from the intervention. 

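### The recruitment target of 24 does not preserve the required 15 at 40% attrition: it covers at most 37.5%, and the calculation leaves out the planned covariates (minor)

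*Protocol article*

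**What the plan says.** The design has one group measured before and after: "This study will use a standard within-participants design, with measurement at pre- and postintervention (1 group, 2 times" (Study Design). The Participants section bases the sample size on "detecting the minimum clinical important difference of 4.0 points [39] on the primary outcome measure (Mini-BESTest", "using an effect size of 0.8, an alpha value of .05, a power value of 80%, and a 2-tailed *t* test". It then moves from the required number to the recruitment target: "We calculated the estimated sample size to be at least 15 participants, which we increased to 24 participants to allow for 40% attrition".

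The third point under Limitations repeats the rate as an expectation: "we expect that 40% of recruited participants will not complete the study intervention due to reasons outside of our control". The fourth says that "while this study is adequately powered, the sample size is still considered small".

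The section Analysis of Test and Questionnaire Data describes a larger model than the one that was powered: "We will include study site and the number of intervention sessions attended by the participants in the statistical model as covariates". It also specifies an intent-to-treat analysis of everyone recruited, with multiple imputation for missing data.

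**The concern.** The protocol gives three figures: a minimum of 15, a target of 24 and attrition of 40%. They cannot all hold, because 24 less 40% is below 15. The target equals 15 × 1.6, whereas allowing for 40% loss means dividing by 0.6.

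The test used for the sample size is also not the planned analysis. With four sites, site takes 3 degrees of freedom, and sessions attended takes 1 if linear. The sample size statement mentions neither.

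At stake is how a non-significant balance result will be read. The power statement and the adequacy claim rest on this calculation, and a reader who takes 80% at face value may give a null result slightly more weight than it can carry.

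**Working it through.** **Inputs.** From Participants: effect size d = 0.8, two-sided alpha .05, target power 80%, difference 4.0 points, minimum 15, target 24, attrition 40%, four sites. From Study Design: one group, paired measurement. From Analysis of Test and Questionnaire Data: site and sessions as covariates. If d is the paired effect size, the implied SD of change is 4.0/0.8 = 5.0; the article does not state it.

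**Formula.** Power = P(|T| > t(0.975, df)), where T is noncentral t with noncentrality d√n. For the paired t test, df = n − 1. With an intercept, three site terms and one sessions term, df = n − 5. The covariates are taken as centred and unrelated to the mean change.

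**Step 1: the protocol's own figure.**
- n = 14: noncentrality 0.8 × √14 = 2.993, df = 13, power 79.0%.
- n = 15: noncentrality 0.8 × √15 = 3.098, df = 14, power 82.1%.

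So 15 is the smallest n that reaches 80%, and the protocol's figure is reproduced.

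**Step 2: allowance for attrition.**
- Expected to remain: 24 × (1 − 0.40) = 14.4.
- Needed to keep 15: 15/(1 − 0.40) = 25.
- Largest attrition at which 24 keeps 15: 1 − 15/24 = 0.375, or 37.5% (9 losses).
- Route to 24: 15 × 1.6 = 24.

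**Step 3: power at the number remaining.** The no-variance column assumes that site and sessions explain none of the variance in change.

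| n with outcome data | Paired t test (df = n − 1) | Site and sessions fitted, no variance explained (df = n − 5) |
|---|---|---|
| 14 | 79.0% | 75.9% |
| 14.4 (fractional) | 80.3% | 77.5% |
| 15 | 82.1% | 79.7% |
| 24 | 96.3% | 96.0% |

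**Step 4: variance explained by the covariates.** Keep the total SD of change at 5.0 and let the covariates explain a share R² of its variance. The effect size becomes 0.8/√(1 − R²). At n = 14 with df = 9:
- R² = 0: 75.9%
- R² = 0.05: 78.0%
- R² = 0.10: 80.1%
- R² = 0.20: 84.5%

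The documents give no value for R², so this is a range under an assumption.

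**The case against.** The strongest reply is that the slip is one participant and hardly changes power. Because 15 already carried 82.1%, the loss leaves 79.0% at 14 and 80.3% at a fractional 14.4. This stands.

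A reader might infer that the trial fails to deliver 80% power on its own assumptions, or that the adequacy claim is false. The documents do not support that, for these reasons:

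- **Covariates.** The 75.9% charges four degrees of freedom and credits no gain in precision. The protocol makes no such assumption, and about 10% explained variance cancels the loss. The article also does not give the form of the model. The net effect on power is therefore unknown in sign.
- **Attrition is not the same as missing outcomes.** Limitations speaks of people who do not complete the intervention, and Participants justifies the rate partly by absenteeism. Inclusion in Data Analysis keeps everyone whatever their attendance, and Procedure has all participants take the posttest. Fourteen with outcome data is thus the pessimistic end. In the other direction, illness and moves to long-term care will cost some posttests, and imputing an unobserved posttest adds little information without strong auxiliary data.
- **Chance of reaching 15.** If retention is binomial with probability 0.6, 24 recruits reach 15 with probability 49%. That looks alarming, but the correct 25 reach it with only 59%. Inflating to an expected number always gives a figure near one half, so this does not show a design failure.
- **SD of change.** The 5.0 follows from the stated difference and effect size. A larger SD would lower power, but any particular larger value would be the reader's own assumption, and an article commonly leaves the source of an SD to the full protocol.

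What remains is that the stated allowance is arithmetically wrong, and that the power quoted is for a simpler test than the planned one.

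**Conclusion.** The point holds as a minor error. The statement that 24 recruits allow for 40% attrition from a minimum of 15 is wrong: the correct target is 25, and 24 covers at most 37.5%. For the stated t test this costs about one percentage point against the 80% target at 14 with outcome data.

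The sample size statement also omits the planned covariates. At 14 they would bring power to 75.9% if they explain nothing, and to about 80% if they explain about 10% of the variance in change. These figures rest on d = 0.8 as a paired effect size (implied SD of change 5.0), on covariates that are centred and unrelated to the mean change, and on every non-completer lacking a posttest. The last of these is pessimistic under the planned intent-to-treat analysis. No estimate, test or analysis set is affected.

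**What to change.** Enrolment is complete, so correct the wording and do not add participants. In Participants, replace the attrition sentence with text to this effect:

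> Twenty-four participants retain at least 15 with outcome data if no more than 37.5% are lost. At 40% loss (14.4, rounded down to 14 with outcome data), power is 79% for the paired t test with d = 0.8 (4.0 points, implied SD of change 5.0). In the model with site and sessions attended it is about 76% if these covariates explain no variance in change, and about 80% if they explain about 10%. Participants who stop sessions but give a posttest are analysed and raise these figures.

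In Limitations, qualify the adequacy claim with the same statement.

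The cost is a text edit and a stated power that becomes slightly less favourable.

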#### MoCA

The MoCA is a brief assessment of global cognitive function [42]. The MoCA assesses individual domains of cognitive function, including attention and concentration, executive functions, memory, language, visuoconstructional skills, conceptual thinking, calculations, and orientation. The MoCA results in scores for the individual cognitive domains that contribute to an overall total. The MoCA is scored out of 30 points, with a score of 25 points or less indicating the presence of cognitive impairment [42]. More specifically, a score of below 23 points on the MoCA indicates MCI [43] and a score of below 17 points indicates Alzheimer disease [44].

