### Procedure

We will first ask potential participants to complete the eligibility screening questionnaire and the MoCA [42] to ensure that the study inclusion criteria are met. The MoCA will be conducted in person, in a quiet and private setting (ie, in a separate room) at each day program. The first author (ED) will be responsible for administering and scoring the MoCA. At this time, prospective participants will also rereview the informed consent with the researcher, who will then determine their capacity to provide informed consent using the decision-making ability and capacity-probing questions. Once a participant has reviewed the informed consent form to their satisfaction, they will be asked to sign the informed consent form in the presence of the researcher, provided that they have the capacity to independently provide informed consent. Given that decisions are time specific, we will review each participants’ capacity to consent on an ongoing basis (ie, at each point of interaction). All consent and assent forms will be signed in a quiet and private area at the day program.

Upon providing informed consent (whether through independent consent or substitute decision-maker consent plus participant assent), each participant will complete the demographic questionnaire and the Mini-BESTest [40]. We will complete the pretest measurements as close to the eligibility measurements and to the intervention as possible (ie, within 1-3 days) to ensure that the MoCA (used for eligibility and outcome purposes) and Mini-BESTest scores do not become outdated. We will conduct the Mini-BESTest in an open area (eg, exercise room) at each day program to ensure that there is enough space to perform the test. Additionally, 2 members of the research team will be present during the Mini-BESTest to ensure that participants can safely perform the test. That is, 1 research team member will evaluate the participants’ performance while the other member acts as a spotter.

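### The entry rule (MoCA ≤25) admits scores of 23 to 25 that the protocol's own MoCA cut-off for MCI does not cover, yet the whole sample is labelled dementia or MCI

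*Protocol article*

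**What the plan says.** **Population.** Participants: "We will recruit a convenience sample of 24 people with dementia or MCI from 4 community-based adult day programs". The objective, hypotheses, Discussion and Conclusions use the same label throughout.

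**Entry.** The one cognitive criterion under Participants is presence of cognitive impairment, "determined by a score of ≤25 on the MoCA". The screening questionnaire notes whether cognitive impairment is present or absent. It does not ask for a diagnosis.

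**Score bands.** The MoCA section gives three thresholds. The first matches the entry rule: "with a score of 25 points or less indicating the presence of cognitive impairment". It then becomes more specific: "a score of below 23 points on the MoCA indicates MCI" and "a score of below 17 points indicates Alzheimer disease".

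**Diagnosis.** Limitations concedes that "the demographic questionnaire developed for this study does not capture" the participants' specific diagnosis or the time since it was made. It treats this as a possible influence on movement confidence and on response to the intervention, not as doubt about who belongs in the population.

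**Use of the MoCA.** Procedure gives the MoCA at screening and lists only the demographic questionnaire and the Mini-BESTest after consent. It describes "MoCA (used for eligibility and outcome purposes". The MoCA is repeated at posttest. Study Design fixes one group measured twice.

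**The concern.** The entry rule and the stated population rest on different thresholds. A person scoring 23, 24 or 25 qualifies, but the protocol's own MoCA band for MCI does not reach that person, and no diagnosis is collected that could. If the plan is followed as written, the Mini-BESTest result will be reported for people with dementia or MCI when an unknown part of the sample has only a positive screen. Readers will not be able to tell how large that part is.

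The second issue is smaller. If one MoCA both selects participants (kept only if 25 or less) and serves as their baseline, people whose score was low by chance are over-represented at baseline. Their retest then rises on average with no effect of the intervention. A single-group design has no comparison to remove this, and the limitations section does not mention it.

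**Working it through.** **The plan's own figure.** The only relevant stated figure is the sample size for the primary outcome. A two-tailed paired t test with effect size 0.8 and alpha .05 has 79.0% power at n = 14 and 82.1% at n = 15, so the stated 15 reproduces. The MoCA entry rule does not enter that calculation. The documents give no figure for the MoCA comparison.

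**Step 1: the thresholds side by side.**
- Entry: 25 or less.
- MCI on the MoCA: below 23, so 22 or less.
- Alzheimer disease on the MoCA: below 17.
- Eligible but above the MCI band: 23, 24 and 25, three score points.

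**Step 2: how many people this could be.** The mean and SD of MoCA in the screened pool are assumptions, because the documents give neither. For a normal pool with mean μ and SD σ, using half-point continuity limits:

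share = [Φ((25.5 − μ)/σ) − Φ((22.5 − μ)/σ)] / Φ((25.5 − μ)/σ)

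For μ = 20, σ = 5: [Φ(1.1) − Φ(0.5)] / Φ(1.1) = (0.8643 − 0.6915)/0.8643 = 0.200, or 24 × 0.200 = 4.8 people.

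**Step 3: regression to the mean in the MoCA change.** With test-retest correlation r (assumed 0.8 to 0.9) and no true change:

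expected change = (1 − r) × σ × φ(c)/Φ(c), where c = (25.5 − μ)/σ

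For μ = 20, σ = 5, r = 0.85: 0.15 × 5 × (0.2179/0.8643) = 0.19 points.

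| Pool mean, SD (assumed) | Share 23-25 | People of 24 | Shift, r = 0.9 | Shift, r = 0.8 |
|---|---|---|---|---|
| 14, 5 | 3.4% | 0.8 | 0.01 | 0.03 |
| 18, 5 | 12.6% | 3.0 | 0.07 | 0.14 |
| 20, 5 | 20.0% | 4.8 | 0.13 | 0.25 |
| 22, 4 | 32.1% | 7.7 | 0.13 | 0.27 |
| 23, 4 | 38.7% | 9.3 | 0.18 | 0.36 |
| 23, 6 | 29.4% | 7.1 | 0.33 | 0.66 |

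At mean 14 with SD 4 both quantities are smaller still (share 1.5%, shift below 0.01).

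**Step 4: effect on the test of Hypothesis 3.** Taking the SD of change as σ√(2(1 − r)) and a noncentral t distribution, the two-sided type I error over pool means 14 to 23 and r 0.8 to 0.9 runs from 5% to 13%. The top value needs mean 23, SD 6, r = 0.8 and all 24 people analysed. At mean 20, SD 5, r = 0.85 it is 5.7% (n = 15) or 6.2% (n = 24).

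**Step 5: does a below-23 subset help the MoCA analysis?** It does not. Replacing 25.5 by 22.5 at μ = 20, σ = 5, r = 0.85 gives 0.15 × 5 × (0.3521/0.6915) = 0.38 points, twice the 0.19 at the entry cut-off.

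**The case against.** **The protocol does not define MCI by a MoCA score.** The Introduction defines MCI and dementia clinically, with no score, and the MoCA section says what a score indicates, not that 23 to 25 rules MCI out. The entry criterion claims only cognitive impairment, which agrees with the MoCA section. This stands. A reader might infer that people scoring 23 to 25 do not have MCI, or that all conclusions must be confined to those below 23. The documents support neither. They show only that the label is unsupported for these people.

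**The admission in Limitations is narrow.** It concerns specific diagnosis and its duration. That is fair, but no diagnosis is required anywhere else, so the gap remains.

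**The sizes are assumptions.** This also stands. The study targets dementia as well as MCI and allows substitute consent, so a low-scoring pool is plausible, and then under one person in 24 is affected.

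**One shared MoCA is an inference.** Procedure speaks separately of eligibility and pretest measurements, and the Abstract lists the MoCA at pretest. The remark that it is used for both purposes, with no second MoCA listed, makes a single score the likelier reading, not a certain one.

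**Regression to the mean is minor.** A reader might infer that Hypothesis 3 is seriously compromised. The figures do not show that. The MoCA is not the primary outcome, the hypothesis predicts a difference without a direction, the shift is mostly a fraction of a point, and decline over 10 weeks could offset it.

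**Conclusion.** The point holds as a mismatch between the entry rule and the population label. Participants scoring 23 to 25 would be reported as having dementia or MCI without support from the protocol's own MoCA cut-off or from any diagnosis collected. The mismatch follows from the text alone. Its size, about 3% to 39% of the sample, rests wholly on an assumed normal pool with mean 14 to 23.

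The regression shift is secondary: upward, about 0.01 to 0.7 points, conditional on one MoCA serving both purposes, on the same assumed pools and on r of 0.8 to 0.9. It calls for cautious interpretation of Hypothesis 3. The Mini-BESTest sample size is unaffected.

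**What to change.** Enrollment is complete, so a separate baseline MoCA after eligibility is no longer available. The following use data already held:

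1. Describe the sample, and word the conclusions, as *screen-positive for cognitive impairment (MoCA ≤25)*.
2. Report the numbers with baseline MoCA below 17, 17-22 and 23-25.
3. Add a sensitivity analysis of the Mini-BESTest in those with baseline MoCA below 23, beside the full-sample result and not in place of it.
4. State whether the screening MoCA is the pretest MoCA. If it is, give the regression shift expected at the ≤25 cut-off, with its assumptions, next to the observed change, and interpret Hypothesis 3 as exploratory.
5. Do not repeat the MoCA change analysis below 23. Selecting harder on the same score enlarges the bias (0.19 to 0.38 points in the example).

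The cost is text edits, one table and one extra analysis. The price is precision: of 15 completers, shares of 3% to 39% leave between 15 × 0.97 = 14.6 and 15 × 0.61 = 9.2 in the subset, below the 15 that the power calculation requires. It should be read as a check on consistency, not as a second test.
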